## 5.6 Statistical Testing of Secondary Endpoints

---

Three secondary endpoints will be tested for superiority in the primary study success analysis as alternative definition of study success. This testing will be performed only if the primary study success testing fails. The statistical significance will be established by one-sided  $\alpha = 0.025$ . Appropriate adjustments will be made to account for impact on Type I error using methods described by Hochberg (1988).

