### 5.4.2 Alternative Definition of Success

---

The alternative definition of success is if ANY of the following secondary efficacy hypotheses has been rejected.

1. One-sided null hypothesis of no superiority of riluzole in change in ASIA Motor Score between the baseline and the 6 months post-surgery.
2. One-sided null hypothesis of no superiority of riluzole in change in Nurick score between the baseline and the 6 months post-surgery.
3. One-sided null hypothesis of no superiority of riluzole in change in NDI score between the baseline and the 6 months post-surgery.

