## 5.5 Statistical Testing of Primary Endpoint (mJOA)

---

The appropriate statistical approach is to test a single one-sided null-hypothesis that the difference between the Investigational and the Placebo arm is equal to or less than 0. Rejection of null-hypothesis is consistent with superiority of investigational treatment.

$$H_0: \mu_i - \mu_c \leq 0$$

$$H_1: \mu_i - \mu_c > 0$$

Where:

$\mu_i$  and  $\mu_c$  are the means of the two independent normal distributions;

$\mu_i$  is the mean population value of the  $\Delta mJOA_{180-b}$  in the patients treated with riluzole;

$\mu_c$  is the mean population value of the  $\Delta mJOA_{180-b}$  in the patients treated with placebo.

The hypothesis will be tested by one-sided t-test at the alpha level of 0.025. If the test value exceeds the nominal critical point, the  $H_0$  will be rejected.

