## 5.7 Sample Size Estimate

---

The required sample size is 270 evaluable subjects, or 135 subjects per study arm. The rationale for the sample size is as follows.

Sample size has been calculated to provide 80% power in testing the primary superiority hypothesis. The estimate has been made by the sample size estimation software package East v5.3 (Cytel, Inc.).

Using the data from the performed CSM study (data on file with the Sponsor), the following empirical estimates have been obtained for the primary outcome parameters.

| Endpoint              | N   | Mean | Standard Deviation |
|-----------------------|-----|------|--------------------|
| $\Delta mJOA_{180-b}$ | 146 | 2.81 | 2.57               |

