**Table 5. Simulation results: difference between investigational and control group is 0.9 absolute points in mJOA**

[figure not shown]

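### Study success can be declared on any of three secondary endpoints after mJOA fails its full one-sided 0.025 test; no alpha is reserved, so the error rate for study success exceeds 0.025

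*Protocol*

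**What the plan says.** Section 5.4 of the protocol defines study success in two ways. The main definition (5.4.1) is rejection of the one-sided mJOA null hypothesis. For that test Section 5.5 says: "The hypothesis will be tested by one-sided t-test at the alpha level of 0.025".

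The second definition is in Section 5.4.2: "The alternative definition of success is if ANY of the following secondary efficacy hypotheses has been rejected". The hypotheses listed are ASIA Motor score, Nurick score and NDI, each as change to 6 months.

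Section 5.6 makes this testing part of the main success analysis: "Three secondary endpoints will be tested for superiority in the primary study success analysis as alternative definition of study success". It sets the order: "This testing will be performed only if the primary study success testing fails". It then states the level afresh ("The statistical significance will be established by one-sided" alpha of 0.025) and adds: "Appropriate adjustments will be made to account for impact on Type I error using methods described by Hochberg (1988"). It does not name the endpoints that the Hochberg adjustment covers.

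The protocol states no error rate for study success under the two definitions together.

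**The concern.** The order in Section 5.6 is the reverse of the usual hierarchy, in which secondaries are tested once the primary has succeeded. Here the primary uses the full 0.025, and its failure gives access to a further 0.025. Under no effect on any endpoint,

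P(study success) = P(mJOA rejected) + P(mJOA not rejected and at least one secondary rejected).

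The first term already takes up the 0.025, or nearly all of it if the futility rule is obeyed. A Hochberg adjustment within the three secondaries caps the chance of a false rejection among them, but does not pay for the alpha already spent on mJOA.

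At stake is what a declared success means. If mJOA failed and the trial were called successful on Nurick, ASIA Motor or NDI, that declaration would come from a procedure whose error rate is above 0.025.

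**Working it through.** **Inputs from the protocol.** One-sided alpha 0.025 for mJOA (5.5) and again for the secondaries (5.6); three secondaries, any one sufficient (5.4.2); difference 0.9, SD 2.57, 135 per arm, 270 in total (5.7, Table 3); z boundaries in Table 4 of 2.5469 for efficacy and 0.9365 for futility at the first look (about 175 subjects), and 1.9896 at the final look (270 subjects).

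**Assumed.** The correlations between the four endpoints. The protocol gives none, so a range is shown, with one common correlation for all pairs.

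**Step 1: reproduce the protocol's own figures, mJOA alone.**

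- Two-look power at a difference of 0.9, by bivariate normal integration: 0.409 at the first look and 0.800 cumulative. Section 5.8 states 40.95% and 80.05%.
- Type I error: 0.0235 with futility obeyed and 0.0250 with futility ignored. Table 4 simulates 2.36%.

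The design for mJOA alone is reproduced and controls its error.

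**Step 2: study success, single look, independent endpoints.** Hochberg on three independent true nulls rejects at least one with probability at most 0.025, so

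1 − (1 − 0.025)² = 1 − 0.950625 = 0.0494, and 0.0494 / 0.025 = 1.98.

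For any correlation at which Hochberg holds its level, the ceiling is 0.025 + 0.025 = 0.05.

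**Step 3: correlated endpoints and the two-look design.** These values come from 2,000,000 simulated trials per correlation with no effect on any endpoint. Hochberg is applied to the three secondaries at 0.025, except in the last row.

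| Chance of declaring study success | corr. 0 | 0.3 | 0.5 | 0.7 |
|---|---|---|---|---|
| Single look | 0.049 | 0.046 | 0.043 | 0.037 |
| Stated boundaries, futility ignored | 0.049 | 0.047 | 0.043 | 0.038 |
| Stated boundaries, futility obeyed, secondaries tested on the data at the stop | 0.048 | 0.044 | 0.039 | 0.033 |
| Stated boundaries, futility obeyed, no secondary test after a futility stop | 0.027 | 0.030 | 0.031 | 0.031 |
| Single look, Hochberg over all four endpoints, mJOA keeping its own 0.025 test | 0.043 | 0.041 | 0.038 | 0.033 |

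At a correlation of 0.9, the single-look rate is 0.029, and the last row gives 0.027. Every case is above 0.025.

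**Step 4: why rows three and four differ.** Under no effect, the first-look statistic falls below 0.9365 with probability 0.825 (Section 5.8 gives 82.5%). Most null trials therefore end at the interim, and whether the secondaries are then tested settles much of the size of the excess.

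**The case against.** Four arguments on the other side deserve an answer.

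**Hochberg may cover it.** Section 5.6 names no family, and Section 5 leaves details to an SAP that is not at hand. A Hochberg procedure over all four endpoints at a total of 0.025 would control the error: it gives 0.0247 at correlation 0 and 0.019 at 0.7. But mJOA would then have to enter that procedure and give up its separate test at 0.025, which Section 5.5 specifies. If mJOA keeps that test, the excess remains (last row of the table). An SAP could repair this only by departing from Sections 5.4.2, 5.5 and 5.6 as written. What stands is that the family is unstated; it should not be reported as limited to the three secondaries by the text.

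**The mJOA claim is sound.** This stands. A reader might infer that the 0.025 in Table 3 is wrong or that a positive mJOA result is in doubt. The documents do not support that. Table 3 concerns the mJOA test only, and that test keeps its level.

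**The futility case is a reading.** A reader might infer that a futility stop is followed by three tests, each at the full 0.025, on interim data. The protocol does not say that the secondaries are tested after such a stop, nor on which data, and Section 5.6 applies an adjustment to them. Table 3 calls futility binding, while Table 4 marks the same item NB. Both ways of handling the stop are therefore shown above.

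**Nearly double is the extreme.** This also stands. The value 0.0494 needs independence, the least plausible case for four measures taken on the same patients at the same visit. At correlations of 0.5 to 0.7, the single-look rate is 1.7 to 1.5 times 0.025 (0.043 / 0.025 and 0.037 / 0.025).

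Nor is testing secondaries after a failed primary wrong in itself. It is valid when alpha is reserved for it in advance; here none is.

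**Conclusion.** The concern holds for study success as defined by Sections 5.4.1 and 5.4.2 together, and not for the mJOA claim. Sections 5.4.2, 5.5 and 5.6 fix a rule whose false-success rate exceeds the one-sided 0.025 in every case computed, from about 0.027 to about 0.049. The lower end applies if the secondaries are not tested after a futility stop; the upper end applies with independent endpoints and futility ignored or a single look. The size rests on assumed correlations and on how a futility stop is handled, which the protocol does not state. The direction rests on neither: a second chance is added to a test that has already been given the whole alpha.

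**What to change.** **Preferred.** Make rejection of the mJOA null the only definition of study success. Test ASIA Motor, Nurick and NDI with Hochberg at one-sided 0.025, naming these three as the family, only if the mJOA null is rejected; otherwise report them descriptively. The false-success rate is then that of the mJOA test, at most 0.025. This means rewording Sections 5.4.2 and 5.6, with no change to sample size or boundaries. The cost is the loss of the second route to success.

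**If the second route must stay.** Split the 0.025 between mJOA and the secondary family in advance, say whether and on which data the secondaries are tested after a futility stop, and restate the power. As an illustration, take 0.020 for mJOA and 0.005 for Hochberg on the three:

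- The error rate is at most 0.020 + 0.005 = 0.025; the single-look simulation gives 0.0249 at correlation 0.
- Fixed-design power at 135 per arm: 0.9 / (2.57 × √(2/135)) = 2.877. Subtracting 1.960 gives power 0.820; subtracting 2.054 gives 0.795.
- Two-look power at 270, with the futility bound held at 0.9365, falls from 0.800 to about 0.778.

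Power thus drops by about 2 to 3 points, to just under the target in Section 5.7 ("Sample size has been calculated to provide 80% power in testing the primary superiority hypothesis"). The boundaries would have to be recalculated and the sample size reconsidered. An even split, with 0.0125 for mJOA, would lower two-look power to about 0.726.

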## 5.7 Sample Size Estimate

---

The required sample size is 270 evaluable subjects, or 135 subjects per study arm. The rationale for the sample size is as follows.

Sample size has been calculated to provide 80% power in testing the primary superiority hypothesis. The estimate has been made by the sample size estimation software package East v5.3 (Cytel, Inc.).

Using the data from the performed CSM study (data on file with the Sponsor), the following empirical estimates have been obtained for the primary outcome parameters.

| Endpoint              | N   | Mean | Standard Deviation |
|-----------------------|-----|------|--------------------|
| $\Delta mJOA_{180-b}$ | 146 | 2.81 | 2.57               |

**Table 3 Sample size estimate  $\Delta mJOA_{180-b}$**

| Plan ID                                           | Parameter          |
|---------------------------------------------------|--------------------|
| Type of the hypothesis                            | 1-Sided            |
| Type I Error ( $\alpha$ )                         | 0.025              |
| Power ( $1 - \beta$ )                             | 0.80               |
| Randomization Ratio (Investigational vs. Control) | 1:1                |
| Planned Number of Interim Looks                   | 2                  |
| Spacing of Looks                                  | 65%, 100%          |
| Hypothesis to be Rejected                         | H0 or H1 (binding) |
| Boundary Family                                   | Published Function |
| Boundary to Reject H0                             | O'Brien-Fleming    |
| Boundary to Reject H1                             | Gamma (-2)         |
| Difference of Means Assuming $H_1$                | 0.9                |
| Standard Deviation ( $\sigma$ )                   | 2.57               |
| Sample Size                                       | 270 (135 per arm)  |

Under the above assumptions, the estimated sample size is 270 evaluable subjects. (135 in the riluzole arm and 135 in the control arm). In order to account for loss of power due to loss of follow-up and possible adjustments for baseline factors we will increase sample size for 10% to **300 enrolled** subjects.

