## 5.8 Statistical Performance and Simulations

The statistical plan aims at efficient design that allows demonstrating efficacy of the treatment while allowing for early stop for futility if the treatment does not appear to be successful.

Figure 1 shows rejection boundaries for H0 and H1 on the absolute delta scale for the interim and the final analysis. The figure shows that the futility stop is at the value of about 0.35 in favor of treatment. In other words, if the difference between the investigational and the control arms is less than 0.35, the study may stop for futility. At the same time, if the difference is about 1.0 absolute point the study may reach efficacy endpoint.

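### Table 3 calls the futility boundary binding, but the printed design is non-binding, and section 5.5 does not say that 0.025 is the overall alpha shared with the interim look

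*Protocol*

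**What the plan says.** - **Section 5.7, text and Table 3.** "Sample size has been calculated to provide 80% power in testing the primary superiority hypothesis". Table 3 gives one-sided alpha 0.025, power 0.80, difference 0.9, SD 2.57, an O'Brien-Fleming boundary to reject H0, a Gamma(-2) boundary to reject H1, and 270 subjects. It places looks at 65% and 100% but counts both as interim looks. The hypothesis to be rejected is "H0 or H1 (binding").
- **Section 5.8, Table 4 design panel.** It has the same alpha, power, difference, SD, spending functions and maximum of 270, but the hypothesis row carries the abbreviation NB. The printed boundaries are z 2.5469 (efficacy) and 0.9365 (futility) at look 1, and 1.9896 at look 2. The unrounded maximum N is 269.64 and the maximum information 10.2060.
- **Section 5.8, text.** "if the difference between the investigational and the control arms is less than 0.35, the study may stop for futility".
- **Section 5.5.** "The hypothesis will be tested by one-sided t-test at the alpha level of 0.025". H0 is rejected "If the test value exceeds the nominal critical point". The section gives no number for that point and mentions neither the interim look nor alpha spending.

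**The concern.** One design cannot have both binding and non-binding futility. The label matters for two reasons.

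First, it decides whether crossing the futility boundary obliges the study to stop. If riluzole has no effect, this is the most likely interim outcome: section 5.8 puts it at 82.5% of simulated trials.

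Second, it sets the final critical value. A binding rule lets the final boundary relax, because trials that cross the futility boundary cannot go on to reject H0. A non-binding rule allows no such credit.

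Section 5.5 does not settle the matter. An analyst who reads 0.025 there as the level of the final test arrives at about 1.96. Table 3's binding label leads to nearly the same value. The only final boundary printed in the protocol is 1.9896.

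**Working it through.** **Inputs.** One-sided alpha 0.025, power 0.80, difference 0.9, SD 2.57, 1:1 allocation and looks at 65% and 100% (Table 3). Lan-DeMets O'Brien-Fleming efficacy spending and Gamma(-2) futility spending (Table 4 panel).

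**Step 1: amounts spent at t = 0.65.**
- Alpha: 2 × [1 − Φ(z₀.₀₁₂₅ / √t)] = 2 × [1 − Φ(2.2414 / 0.8062)] = 0.00543, so the interim efficacy boundary is z = 2.5469, as printed.
- Beta: 0.20 × (1 − e^(2t)) / (1 − e^2) = 0.20 × (−2.669 / −6.389) = 0.0836. With drift d at full information, the futility boundary is Φ⁻¹(0.0836) + d√0.65.

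**Step 2: final boundary c and drift d.** The joint distribution of the two statistics has correlation √0.65. Solve for c so that total alpha is 0.025, and for d so that power is 0.80. Then N = 4 × (d × 2.57 / 0.9)² and information = d² / 0.9². For the alpha calculation, the non-binding design lets paths below the futility boundary continue; the binding design removes them.

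| | Non-binding | Binding | Printed in Table 4 |
|---|---|---|---|
| Drift d | 2.8752 | 2.8464 | – |
| Interim efficacy z | 2.5469 | 2.5469 | 2.5469 |
| Interim futility z | 0.9365 | 0.9133 | 0.9365 |
| Final z | 1.9896 | 1.9594 | 1.9896 |
| Nominal one-sided p at the end | 0.0233 | 0.0250 | – |
| N | 269.64 | 264.25 | 269.64 |
| Information | 10.206 | 10.002 | 10.2060 |

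For example, 4 × (2.8752 × 2.57 / 0.9)² = 269.6, and 4 × (2.8464 × 2.57 / 0.9)² = 264.3. The non-binding column matches every printed figure. In the binding column only the interim efficacy boundary matches, and that boundary does not depend on the futility rule.

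**Step 3: type I error**, with interim efficacy boundary 2.5469 and futility boundary 0.9365.

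| Final critical value | Futility obeyed | Futility overruled |
|---|---|---|
| 1.9896 | 2.35% | 2.50% |
| 1.96 | 2.48% | 2.66% |

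Table 4 simulates 2.36%, which agrees with the 2.35%. That agreement is weak evidence by itself: the simulation error is √(0.0236 × 0.9764 / 10,000) = 0.15 percentage points. The boundaries, N and information are what separate the two designs.

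**Step 4: mJOA scale at N = 270.** The standard error is 2.57 × √(4 / 270) = 0.3128. The threshold is 1.96 × 0.3128 = 0.613 or 1.9896 × 0.3128 = 0.622, a difference of about 0.009 points.

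**Step 5: power at 0.9 points and N = 270, futility obeyed.** It is 80.05% with 1.9896, the cumulative figure that section 5.8 reports, and 80.7% with 1.96.

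**The case against.** The best defence is that the protocol prints only one final critical value, 1.9896. Table 3 lists 0.025 as the type I error beside a two-look boundary, so 0.025 is naturally the overall alpha. The unnumbered critical point in 5.5 can then be read as the group-sequential boundary, which removes any conflict over the threshold. Section 5 also leaves details to the SAP. This stands as a possible reading, but 5.5 does not state it, and it does not reconcile the two futility labels. An SAP cannot agree with both.

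Each design used consistently also controls the error. Binding with 1.9594 gives 2.5%, and non-binding with 1.9896 gives at most 2.5%. Exceeding 2.5% takes two departures together: about 1.96 at the end, and an overruled futility stop. That is correct and limits the size of the point.

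The word may in 5.8 is weak evidence for non-binding futility, because the same paragraph uses it for reaching efficacy. The conclusion does not rest on it.

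Three stronger readings are tempting, and the documents do not support them:
- **A reader might infer that two different final critical values are printed.** They are not. The 1.96 is only implied, by 0.025 in 5.5 and by the binding label.
- **A reader might infer from 5.5 that 0.025 applies at both looks, with a larger inflation.** Section 5.5 describes no interim test, Table 4 prints 2.5469 for it, and 5.8 places interim efficacy at a difference of about 1.0. A z of 1.96 there would be 1.96 × 2.57 × √(4 / 175.5) = 0.76 points.
- **A reader might infer that the 270 is wrong.** It is the rounded non-binding result. Under binding futility it would exceed the need by about 2% (270 against 264.25), so power is not at risk.

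**Conclusion.** The point holds. Table 3's binding label contradicts Table 4, and the calculation shows that the label is what is wrong: the printed design is non-binding. Section 5.5 adds a real ambiguity, because it does not identify 0.025 as the overall alpha or say which final boundary applies.

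The numerical effect is small. In the worst mixed case the type I error is 2.66%, which is 0.16 percentage points above the stated level, and the threshold moves by about 0.009 mJOA points. The practical weight lies in the unsettled status of a futility boundary that a null drug would usually cross, and in a borderline final statistic between 1.96 and 1.99.

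These figures assume an interim look at exactly 65% information, a normal approximation with SD 2.57, and no change of sample size under 5.9.

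**What to change.** - **Table 3:** label the hypothesis row H0 or H1 (non-binding), and give the looks as two in total, one interim at 65% and one final.
- **Section 5.5:** state that 0.025 is the overall one-sided alpha under Lan-DeMets O'Brien-Fleming spending. Give the planned boundaries as z 2.5469 at 65% and z 1.9896 at the end (nominal p 0.0054 and 0.0233), recomputed for the actual information fraction.
- **Link to section 5.9:** add that, if the sample size is changed after the interim, the final test uses the alpha-preserving adaptive method specified in the SAP. Section 5.9 lets the re-estimate depend on the observed effect, so recomputing the information fraction would not protect the error rate by itself.

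The cost is wording in two places, best settled before the interim analysis. The 270 and the 80% power are unchanged. The final threshold becomes slightly stricter than a literal reading of 5.5.

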## 5.8 Statistical Performance and Simulations

The statistical plan aims at efficient design that allows demonstrating efficacy of the treatment while allowing for early stop for futility if the treatment does not appear to be successful.

Figure 1 shows rejection boundaries for H0 and H1 on the absolute delta scale for the interim and the final analysis. The figure shows that the futility stop is at the value of about 0.35 in favor of treatment. In other words, if the difference between the investigational and the control arms is less than 0.35, the study may stop for futility. At the same time, if the difference is about 1.0 absolute point the study may reach efficacy endpoint.

**Figure 1 Rejection boundaries for mJOA**

[figure not shown]

Table 4 shows simulation results of the testing under the assumption of no difference between the investigational and control groups. The simulation shows that under those conditions, the H1 will be rejected in 82.5% of the cases at the interim analysis (futility stop) and at 97.64% cases at the final analysis.

Table 5 shows simulation results of the testing under the assumption of a treatment effect of the size of 1 absolute point in mJOA, the background for the sample size estimate. The simulation shows that under those conditions, the H0 will be rejected in 40.95% of the cases at the first interim analysis, and in cumulative 80.05% at the last analysis.

Efficacy of Riluzole in Patients with Cervical Spondylotic Myelopathy Undergoing Surgical Treatment. A Multi-Center Double Blind Randomized Controlled Study.

